### **3.6. Outliers**

Outliers of non-PK data will be identified during the data management and data analysis process, but no sensitivity analyses will be conducted. All data will be included in the data analysis.

### **3.7. Definitions**

#### **3.7.1. Study Day**

Study Day 1 refers to the date of initial administration of the study intervention (TLC-2716 or placebo). Other study days are defined relative to Study Day 1, and previous days to Study Day 1 are expressed as Day -1 or Day -2 (there is no Study Day 0). Note, in the event an entire cohort is administered placebo on a day prior to Day 1 (e.g., Day -1) for the purposes of supporting additional exploratory biomarker or PD assessments, Day 1 will remain the day upon which randomized subjects are considered to have received TLC-2716 or placebo.

#### **3.7.2. Baseline**

Baseline is defined as the last value obtained before the administration of study intervention (TLC-2716 or placebo), unless otherwise stated. For laboratory data, baseline will be Day -1 for all cohorts in Parts A, B, and C. For ECG parameters, baseline will be Day -1 for SAD Cohorts in Parts A and C, and Day -2 for MAD cohorts in Parts B and C.

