Within Part A and SAD cohorts in Part C, initiation of single-dose administration at escalating dose levels will be determined by evaluation of cumulative safety data, and available and relevant PK and PD data up to and including Day 4, following single-dose administration of the previous dosing cohort. Similarly, in MAD cohorts in Parts B and C, initiation of multiple-dose administration at a higher dose level will be determined by evaluation of safety and available PK and PD data from all subjects enrolled through Day 14 of the previous dosing cohort. Additionally, in adaptive cohorts in Part C, sentinel dosing will be utilized in any cohort wherein the total daily dose to be administered is greater than has previously been evaluated. In these multiple-dose cohorts, to support a comprehensive evaluation of the relationship between TLC-2716 PK and PD, all subjects regardless of treatment assignment will be administered placebo capsule(s) on Day -1 to characterize the baseline daily variation of PD markers for subsequent comparison with changes that occur during dosing of TLC-2716 or PTM from Day 1 through 14. Additional details regarding dose escalation criteria are provided in Section 3.2.

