## **5.3. Administration of Study Drug**

In Parts A and B, all study treatments will be administered orally at the study center in the morning at approximately the same time each day, within 5 minutes of completing a standardized meal, and with water. The standardized meal should be initiated 30 minutes prior to study drug administration. Except for the water provided with the study drug(s) and water or

beverages with the standardized meal, subjects will be restricted from water consumption from 1 hour before through 2 hours after dosing.

In Part C, study drug may be administered in a fed or fasted state, QD or BID (BID only in MAD cohorts). In the case of QD dosing in fed state, study drug should be administered as in Parts A and B described above. In the case of fasted state or BID dosing, please see Section 5.3.1 for instructions.

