#### **6.6.1. Plasma and/or Serum Pharmacodynamic Assessments**

Blood samples will be collected to measure PD biomarkers for TLC-2716 at the time points described below, where '0' indicates the pre-dose time point in the morning. Blood samples for PD assessments will be collected in the same subject order on each day, including the pre-dose

day, in each cohort. For MAD cohorts, the collection times on the day prior to the dosing day (e.g., Day -1) must match those on the days of subsequent dosing ( $\pm 5$  minutes).

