**MAD Cohorts in Parts B and C:**

Day -1: (all  $\pm 5$  minutes of Days 1, 7, and 14 time points), 0, 2, 4, 6, and 12 hours

Days 1, 7, and 14: Pre-dose ( $\leq 10$  minutes prior to dosing), and 2, 4, 6, and 12 hours post-dose

All post-dose timings above are relative to the morning dose for QD or BID dosing. In the case of BID dosing in Part C, the 12 hours post-dose time point must be collected prior to the second daily dose of the study drug.

Sampling time points may be modified by the sponsor based on emerging data and assay feasibility.

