## **9. PHARMACODYNAMIC ANALYSIS**

Exploratory descriptive analysis of PD markers collected in this study, including absolute and relative (percent) changes from baseline, may be evaluated.

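### MAD cohorts collect a clock-matched Day -1 placebo profile of PD markers, but the SAP's PD baseline is one pre-dose value, so 2-12 h PD changes combine drug effect with meal and time-of-day variation

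*Combined protocol and SAP*

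**What the plan says.** Protocol 1.3.1 explains the Day -1 placebo in multiple-dose cohorts: "all subjects regardless of treatment assignment will be administered placebo capsule(s) on Day -1 to characterize the baseline daily variation of PD markers". The stated use is later comparison with changes seen on Days 1 to 14.

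Protocol 6.6.1 sets Day -1 PD draws at "0, 2, 4, 6, and 12 hours", with the same nominal times on Days 1, 7 and 14. It requires that "the collection times on the day prior to the dosing day (e.g., Day -1) must match those on the days of subsequent dosing", within 5 minutes. Protocol 6.6.3 gives the exploratory biomarkers the same schedule.

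SAP 3.7.2 defines baseline generally: "Baseline is defined as the last value obtained before the administration of study intervention (TLC-2716 or placebo), unless otherwise stated". Its stated exceptions are laboratory data (Day -1) and ECG (Day -1 in single-dose cohorts, Day -2 in MAD cohorts). SAP 3.7.1 keeps Day 1 as the first day of study intervention even when a whole cohort takes placebo the day before.

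SAP 9 is a single sentence. Descriptive analysis of PD markers, "including absolute and relative (percent) changes from baseline, may be evaluated". It names no other baseline. Protocol 8.8 lists and summarises PD data by cohort, treatment group and individual sampling time.

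On meals, Protocol 5.3 says of fed dosing: "The standardized meal should be initiated 30 minutes prior to study drug administration".

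**The concern.** The Day -1 placebo day gives each subject a drug-free curve at the hours sampled later on treatment. The analysis that follows from that design compares 4 h on Day 14 with 4 h on Day -1. The SAP default compares 4 h on Day 14 with one morning pre-dose value, so whatever the marker does naturally between morning and 4 h is counted as change from baseline.

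The protocol recognises the issue: section 1.3 notes that diet can affect serum lipids, and section 8.8 anticipates summaries of the effect of food on PD biomarkers. ANGPTL3, ApoC3 and lipogenesis markers at 2-12 h are the readouts exposed. They are exploratory, but Protocol 1.3 says that PD data from this study will inform dose selection for Phase 2. A within-arm change that partly reflects breakfast is a poor basis for that choice.

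**Working it through.** **Step 1: which value is the PD baseline?** SAP 3.7.2 gives the last value before study intervention. SAP 3.7.1 makes Day 1 the first intervention day. For a MAD subject the PD baseline is therefore the Day 1 pre-dose sample. SAP 3.4.1 places the doses differently (treatment on Day -1, MAD placebo on Day -2), which conflicts with SAP 3.7.1 and with the dosing table in Protocol 3.1.2. On either reading the baseline is one value, not a profile.

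**Step 2: where does that value sit relative to the meal?** The pre-dose PD draw is at most 10 minutes before dosing. In fed cohorts the meal starts 30 minutes before dosing. The draw therefore falls at least 30 - 10 = 20 minutes after the meal begins, during it or just after it. The 2-12 h samples then follow the post-meal course.

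**Step 3: what does each definition estimate?** Let *m* be the natural ratio of the marker at hour *t* to its pre-dose value, and *r* the true drug ratio.

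- Change from the single pre-dose value: *r* × *m* - 1
- Change from Day -1 at the same hour, if the daily pattern is stable: (*r* × *m*) / *m* - 1 = *r* - 1

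The documents give no value for *m*. The values below are assumptions for illustration.

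| Assumed natural change at hour *t* | No drug effect (*r* = 1.0): single baseline | Time-matched | True -20% (*r* = 0.8): single baseline | Time-matched |
|---|---|---|---|---|
| -20% | -20% | 0% | -36% | -20% |
| +10% | +10% | 0% | -12% | -20% |
| +30% | +30% | 0% | +4% | -20% |
| +50% | +50% | 0% | +20% | -20% |

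For example, 0.8 × 1.3 - 1 = +4%.

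**Step 4: what if the pattern is not stable?** If the natural level at that hour shifts by a factor *d* between Day -1 and the dosing day, the time-matched change is *r* × *d* - 1. With *d* = 1.1 and *r* = 0.8 this is 0.88 - 1 = -12%. Time-matching does not remove such drift. Dividing by the placebo ratio does, if placebo subjects share the drift.

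**Step 5: could the placebo arm do the job alone?** Assume equal SD of the change in both arms. The standard error of active minus placebo is SD × √(1/n₁ + 1/n₂).

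- One cohort, 8 against 2: √(1/8 + 1/2) = 0.79 SD
- One active group against Part B placebo pooled, 8 against 5 × 2 = 10: √(1/8 + 1/10) = 0.47 SD

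Neither document specifies this contrast for PD markers. Protocol 8.3.1.3 limits each PD set to subjects who received TLC-2716, so as worded it leaves placebo subjects out. SAP 2 defines no PD set.

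**Step 6: what is collected?** If all five Part B cohorts run, 50 subjects × 4 times (2, 4, 6 and 12 h) = 200 Day -1 post-placebo time points per marker enter no defined change.

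**The case against.** The strongest answer is that the Day -1 data are in the plan. A reader might infer that no planned analysis uses them, and that is wrong: Protocol 8.8 summarises PD data at individual time points by treatment group, so Day -1 means appear alongside the same hours on Days 1, 7 and 14. With complete data a mean absolute change can be worked out from those tables. The SD of the within-subject change and the mean percent change cannot. What is missing is a defined time-matched change.

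A reader might also infer that the main lipid results are distorted. The documents do not support this. Protocol 6.6 has serum lipids drawn fasting before the morning meal, apart from 12 h on Day 1. SAP 6 analyses fasting triglycerides, total cholesterol, LDL-C and HDL-C, which as laboratory data have a Day -1 baseline. Likewise, pre-dose on Day 7 or 14 against pre-dose on Day 1 is already matched for hour and meal position.

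Two further points stand in part. SAP 9 only says that changes may be evaluated, so no test or decision rule depends on them. And a meal curve shared by all arms would be visible in placebo subjects. But that comparison is unplanned, is imprecise within a cohort, and conflicts with the PD set as worded.

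The phrase allowing for exceptions in SAP 3.7.2 does not help, because SAP 9 states none for PD.

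**Conclusion.** The concern holds for non-fasting PD and exploratory biomarkers at 2-12 h in MAD cohorts. For these the SAP's baseline does not carry out the comparison for which the protocol introduced the Day -1 placebo, and a change computed as written mixes drug effect with meal and time-of-day variation.

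The size cannot be derived from the documents; the table above shows only how an assumed excursion carries through.

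A reader might infer that time-matching would bring the natural component to zero. That requires the daily and meal pattern to be stable from Day -1 to Days 1, 7 and 14, which the documents do not establish. Day -1 follows admission by one day, whereas Day 14 comes after two weeks of confinement. Protocol 5.3.1 also extends the post-dose fast to the 4 h sample on PK days and to 2 h on other days, and Day -1 has no PK sampling, so meals on Day -1 may not line up at 4 and 6 h. This is why the difference from placebo is needed as well.

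The endpoints are exploratory and descriptive, so the correction is worth making before analysis but does not affect the primary safety and PK objectives.

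**What to change.** In SAP 3.7.2 and SAP 9:

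- State that for PD and exploratory biomarkers in MAD cohorts, baseline at each nominal time (0, 2, 4, 6, 12 h) is the Day -1 value at the same nominal time.
- Report the time-matched absolute and percent change on Days 1, 7 and 14, and its difference from pooled MAD placebo. If fasted MAD cohorts are run in Part C, pool placebo within the same meal condition.
- Define a PD analysis set that includes placebo subjects, and correct Protocol 8.3.1.3 to agree.
- Keep the Day 1 pre-dose baseline for NMR LipoProfile and whole-blood ABCA1 and ABCG1 mRNA, which have no Day -1 sample. Interpret their post-dose changes against placebo.
- Reconcile SAP 3.4.1 with SAP 3.7.1 on the days of the placebo and first treatment doses.
- Record which of the Protocol 5.3.1 fasting rules applied on Day -1, so that the matching at 4 and 6 h can be judged.

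The cost is SAP wording, the matching protocol correction and programming. No new samples or visits are needed. SAP 1 already provides for documenting later changes in the clinical study report.

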## **4. DEMOGRAPHIC AND OTHER BASELINE CHARACTERISTICS**

### **4.1. Subject Disposition**

The following analyses will be performed for all randomized subjects.

The number and proportion of subjects who completed the study, and the number of subjects who discontinued the study will be determined. In addition, the reason for discontinuation from the study will be summarized by cohorts and treatment interventions.

The number and proportion of subjects in each analysis population will be summarized as well as the reasons for exclusion from each analysis population.

The number and proportion of subjects who met important protocol deviation categories will be summarized with the reason for deviation by cohorts and treatment interventions.

### **4.2. Demographic and Baseline Characteristics**

Subject demographic variables (i.e., age, sex, race, and ethnicity) and baseline characteristics (body weight [in kg], height [in cm], body mass index [BMI; in kg/m^2]) will be summarized for each cohort, including pooled placebo subjects, in Parts A, B, and C. The summary of demographic data will be provided for the Safety Analysis Set.

A by-subject demographic listing, including the informed consent date, will be provided by subject ID number in ascending order.

### **4.3. Medical History**

Medical history data will be collected at Screening and listed only. A by-subject listing of general medical history will be provided by subject ID number and onset date in chronological order. The listing will include relevant medical condition or procedure reported term, onset date, ongoing status, and resolution date, if applicable.

## **5. STUDY CONDUCT**

### **5.1. Prior and Concomitant Medications/Therapies**

Prior medications/therapies are defined as medications/therapies which have been taken prior to administration of study intervention. Concomitant medications/therapies are defined as medications/therapies taken at or after administration of study intervention. Prior and concomitant medications will be coded using the latest version of the WHO Drug Global Dictionary.

For the Safety Analysis Set, a by-subject listing of prior and concomitant medications/therapies will be provided by subject ID number and administration date in chronological order.

### **5.2. Treatment Exposure and Compliance**

A subject's extent of exposure to study drug data will be generated from the study drug administration page in the eCRF. Exposure data will be listed.

Total days of administration is defined as total number of days of study drug administration (TLC-2716 or placebo).

Treatment compliance rate will be summarized descriptively by cohorts and treatment interventions for the Safety Population. Treatment compliance rate is defined as:  $[100\% * [(total\ days\ of\ administration) * (total\ days\ of\ planned\ administration)]]$ .

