### **3.4. Duration of Dosing**

The duration of dosing for each part will be as follows:

Part A (SAD): 1 day

Part B (MAD): 15 days (including PTM dosing for all subjects on Day -1)

Part C (Adaptive SAD and/or MAD): 1 or 15 days (including PTM dosing for all multiple-dose subjects on Day -1)

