## **8.10. Sample Size**

Due to its exploratory nature and no reliable variability estimation, no formal power or sample size calculations were used to determine the sample size for this study. Empirically, a sample size of 100-150 subjects (10 subjects per cohort, including 8 active and 2 placebo) was selected to provide an adequate characterization of safety, PK, and PD of TLC-2716.

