### 1.2.2. Part B: Multiple-Ascending Dose [MAD] (Cohorts 6-10)

Part B will proceed in up to 5 dose-escalation cohorts and will be governed by reviews of safety and tolerability, and any relevant and available PK and/or PD data, and study-specific stopping criteria. Within each cohort, 10 unique subjects will be randomized 4:1 to receive either blinded TLC-2716 (N = 8) or PTM (N = 2) QD for 14 days.

All study drugs in Part B will be administered in the morning following a standard meal.

Part B (Cohort 6) may be initiated after the evaluation of cumulative safety, tolerability, and any relevant and available PK and/or PD data from all subjects enrolled in Cohort 3 in Part A (up to and including Day 4).

For Cohorts 7-10, dosing may be initiated after evaluation of cumulative safety, tolerability, and any relevant and available PK and/or PD data from all subjects enrolled in the previous cohort in Part B through Day 14.

In both Parts A and B, escalation to a dose higher than previously studied may occur only in the absence of dose-limiting toxicity and/or not meeting any prespecified stopping criteria.

The cohorts and study treatments for Part B are as follows:

| Cohort | Day -1         | Days 1-14                                                 |
|--------|----------------|-----------------------------------------------------------|
| 6      | PTM capsule SD | 0.5 mg TLC-2716 (1 x 0.5 mg) or PTM capsule, fed          |
| 7      | PTM capsule SD | 2 mg TLC-2716 a (1 x 2 mg) or PTM capsule, fed |

| Cohort | Day -1          | Days 1-14                                                             |
|--------|-----------------|-----------------------------------------------------------------------|
| 8      | PTM capsules SD | 6 mg TLC-2716 a (3 x 2 mg) or PTM capsules, fed            |
| 9      | PTM capsules SD | 12 mg TLC-2716 a (2 x 5 mg; 1 x 2 mg) or PTM capsules, fed |
| 10     | PTM capsules SD | 20 mg TLC-2716 a (4 x 5 mg) or PTM capsules, fed           |

PTM = placebo-to-match; SD = single dose.

a The planned doses may be modified based on the observed safety, tolerability, and any relevant and available PK and/or PD data. Any modified dose will be within 3-fold of a dose previously tested.

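### SAP 5.2 defines the treatment compliance rate as a product instead of a ratio, so the planned summary is wrong for every multiple-dose subject (19,600% for full compliance over 14 days).

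*Combined protocol and SAP*

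**What the plan says.** SAP 5.2 gives the rate as 100% multiplied by "total\ days\ of\ administration) * (total\ days\ of\ planned\ administration". It defines the first term: "Total days of administration is defined as total number of days of study drug administration (TLC-2716 or placebo". It does not define planned days. The use is also stated: "Treatment compliance rate will be summarized descriptively by cohorts and treatment interventions for the Safety Population". (SAP 2.2 calls that population the Safety Analysis Set.)

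The number of planned days comes from other sections. For Part B, SAP 1.2.2 has subjects randomized to "either blinded TLC-2716 (N = 8) or PTM (N = 2) QD for 14 days". For single dosing, protocol 3.4 has "Part A (SAD): 1 day". The same protocol section also gives a longer count for multiple dosing that takes in the placebo given to everyone the day before: "Part B (MAD): 15 days (including PTM dosing for all subjects on Day -1".

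The only other text on exposure, protocol 8.6.1, says that exposure data come from the eCRF and will be listed. It gives no compliance formula.

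**The concern.** A percentage called a compliance rate can only be read as the share of planned treatment that was taken. A product of two day counts is not a share, and its value grows with the square of the planned duration. The SAP is the only place where the derivation is written down, and it commits to a table built on it. A programmer who follows the text would produce values in the thousands of percent for all of Part B and for any multiple-dose cohort in Part C.

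Changing the operator also brings up two questions that the section leaves open: whether the Day -1 placebo dose counts, and how a twice-daily day with one missed dose counts.

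**Working it through.** The SAP states no numerical compliance value, so there is no document figure to reproduce. The check is direct arithmetic on the printed formula.

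Inputs:
- Planned randomized days: 14 in Part B (SAP 1.2.2) and 1 in Part A (protocol 3.4).
- Planned days if the Day -1 placebo is counted: 15 (protocol 3.4).
- Planned doses in a twice-daily Part C cohort: 2 x 14 = 28.

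Formulas, with t = days taken and p = days planned:
- As written: 100 x t x p
- As a rate: 100 x t / p

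| Taken | Planned | As written | Ratio |
|---|---|---|---|
| 1 | 1 | 100% | 100% |
| 14 | 14 | 19,600% | 100% |
| 13 | 14 | 18,200% | 92.9% |
| 7 | 14 | 9,800% | 50.0% |
| 1 | 14 | 1,400% | 7.1% |
| 15 | 15 | 22,500% | 100% |

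The printed value divided by the true rate is (t x p) / (t / p) = p². For p = 14 this is 196, the same for every subject. So the scale is wrong but the ordering is preserved in once-daily cohorts. For p = 1 the factor is 1, which is why single-dose values are right.

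**Day -1 placebo, after the operator is corrected.** If Day -1 entered the numerator while 14 stayed in the denominator, full compliance would be 15/14 = 107.1%, and a subject who missed one randomized day would score 14/14 = 100%. If it were counted on both sides, full compliance would be 15/15 = 100% and one missed day 14/15 = 93.3%. If it is excluded, one missed day is 13/14 = 92.9%.

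**Twice-daily dosing, after the operator is corrected.** A subject who misses one of 28 doses still has 14 days with administration. The day count gives 14/14 = 100%; the dose count gives 27/28 = 96.4%. In the limiting case of every evening dose missed, the figures are 100% and 14/28 = 50%.

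**The case against.** The strongest reply is that this is an obvious slip in a descriptive table. The intent is clear, and 19,600% would be noticed at the first output. That bears on weight. It does not make the written rule correct.

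A reader might infer more than the documents support, in four ways.

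- **That the table could not show a missed dose.** In a once-daily cohort it could: the printed value is the true rate times 196, so 18,200% against 19,600% still marks the missed day.
- **That multiple-dose PK would be compromised.** Nothing downstream uses the rate. It is not among the endpoints in protocol 8.1.2 or 8.1.3, it defines no analysis set in SAP 2, and it enters none of the PK models in SAP 8.1.4 to 8.1.6. Under protocol 5.4 centre staff give each dose and record it, and exposure is listed by subject, so a missed dose stays traceable.
- **That the Day -1 placebo dose counts toward compliance.** SAP 3.7.1 keeps Day 1 as the start of randomized treatment even when a whole cohort receives placebo the day before, and footnote n of the multiple-dose schedule separates the Day -1 placebo from study drug starting on Day 1. The 15 days in protocol 3.4 describe duration of dosing, not compliance. A clarifying phrase is enough.
- **That the twice-daily point is part of the same error.** It is a separate limitation and matters only if an optional Part C cohort with that schedule is run. The limiting case is remote: dosing is supervised, and protocol 3.1.3 requires both doses on Day 14.

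The text was read from a PDF by a program, so a misread operator cannot be wholly excluded. Division signs in the PK parameter definitions of SAP 8.1.3 came through intact, which makes a misread unlikely, but the source page should be checked.

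**Conclusion.** The formula in SAP 5.2 is wrong as written. It gives a wrong value for every dosed multiple-dose subject, inflated by a factor of 196 where 14 days are planned, and a correct value only for single-dose subjects. The error reaches one planned descriptive summary and goes no further: inference, sample size, analysis sets and PK results are unaffected. It is worth correcting because it is an analysis rule in the body of the SAP, with no correct version elsewhere to fall back on.

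This rests on the asterisk being in the source document. If the PDF shows division, the main point falls and only the Day -1 clarification and the conditional twice-daily point remain.

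**What to change.** Replace the formula in SAP 5.2 with: compliance rate = 100 x (days of administration from Day 1) / (days planned from Day 1), with 1 planned day in single-dose cohorts and 14 in once-daily multiple-dose cohorts. Add that the Day -1 placebo dose is excluded from both terms, consistent with SAP 3.7.1. Add that in any twice-daily Part C cohort the numerator and denominator count doses, with 28 planned. In the same edit, name the population as the Safety Analysis Set, as in SAP 2.2.

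The cost is a line or two of SAP text. No new data are needed: administration is already recorded, and the planned counts restate the regimens already in the documents.
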